Patients will be randomized by a form of adaptive randomization, called minimization, because simple randomization could result in covariate imbalances (63). Statistical adjustment of covariates can take imbalances into consideration, but results are generally more credible when they are obtained from groups with comparable baseline distributions. In minimization, group assignment is done sequentially. In this study, the patient characteristics used for group assignment will be stage of disease, age (running mean), sex, the mean planned parotid doses (left and right side will be calculated separately and balanced between groups; <10, 10-<20, 20-<26, 26-<30, 30-<35, 35-<40, 40-<50, 50-<60, ≥60), induction therapy (yes/no), and concurrent chemotherapy (yes/no). Randomization will be conducted at each site separately. This will ensure equal distribution of all factors across all groups and balanced at each site. Information on group assignment will be only communicated to the acupuncturists by the data managers to insure that the research staff remains blinded.

Treatment will be withheld if lab values are not within an acceptable range (ANC>500; platelet count>20K/ml; INR, 3.0); if the study participant is diagnosed with a mental incapacitation or significant emotional or psychiatric disorder that interferes with his/her ability to cooperate with study procedures; or if a participant receives any heparin or warfarin during the treatment period.

Participants will be dropped from the study, at any point during the study, if the participant begins taking a prohibited medication (Appendix F) or if the participant encounters a cerebrovascular accident or spinal cord injury.

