### **a. Data analysis**

Our primary objective is to determine if true acupuncture is more effective than sham acupuncture or standard care for preventing radiation-induced xerostomia among cancer patients at M. D. Anderson and Fudan Cancer Hospital. The primary outcome will be self-reported xerostomia symptoms using the Xerostomia Questionnaire (XQ). We will have information available at baseline and at 5 additional points in time (middle of radiotherapy, end of radiotherapy, and 2-4, 5-9, and 10-15 months after the end of radiotherapy).

Our initial analysis will be a repeated-measures analysis of XQ scores over time by acupuncture group, testing for group effects, time effects, and group by time interaction. This will be done using generalized linear mixed model regression (GLMM) (see below for further details). The primary significance level which will be used is

0.05. For sample size justifications, our primary time endpoint is the end of radiotherapy, or 7 weeks. All three arms will be compared at this time point using an analysis of variance, and if the test is significant ( $p < 0.05$ ), we will use a Duncan's Multiple Range Test which controls the type I comparison-wise error rate to determine which groups are different from each other.

At each point in time, we will also be able to determine if xerostomia has occurred (grade 1 or higher on the v3.0 CTCAE) and will classify each patient as either experiencing xerostomia (one or more episodes of xerostomia) or not. A secondary goal is to determine if the proportion of persons who experience xerostomia in the true acupuncture group is less than that in the sham acupuncture group or the standard care group. We will use the

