binomial test to test for these differences at each follow-up. We will also use the clinical response criteria of determining whether or not xerostomia has occurred or not as used by Eisbruch (22) and Pacholke (74). A significant response will be indicated if the summation XQ score  $\leq$  is 30. Eisbruch and colleagues revealed with bilateral radiation therapy treatment, the peak effect of XQ xerostomia scoring at 3 months post treatment is 45 +/- 10 (22). Using the criteria of  $\leq$  30 on the XQ score, we will use the binomial test to test for these differing proportions between groups at each follow-up. However, if 15 tests are made, in order for the results to be considered as significance as those with a 0.05 significance level, the significance level would need to be 0.003 or less (0.05/15) using a conservative Bonferroni method. We will also include a GLMM analysis to evaluate treatment and time effects upon incidence (general patterns in incidence). This analysis will test the overall treatment effect, the overall time effect and a treatment by time effect.

Other outcomes include the MDASI-HN, FACT-G, USFR, SSFR, and saliva constituents including pH, buffering capacity, and viscosity as well as levels of total protein, CGRP, and VIP. These variables are repeated measurements on multiple outcomes, possibly including hierarchical structure over subscales and related outcome measures. Desired inference includes hypotheses about treatment effects at different times and on different outcomes. Also, inference about treatment effects has to appropriately adjust for recorded baseline characteristics of the enrolled patients. With these considerations in mind, we propose the following strategy for the data analysis of these variables. As we expect scores on the criterion measures to be correlated within individuals over time, we will use GLMM. Separate sets of analyses will be conducted for each criterion variable (e.g., primary outcome: severity of self-reported xerostomia symptoms (XQ); secondary outcomes: MDASI-HN, FACT-G, saliva flow rates, and saliva constituents). For each criterion variable, we will use data across the set of post-intervention assessment points. In modeling these data, intervention condition is a between-subjects factor, time is a within-subjects factor, and baseline measures will be included as covariates.

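### The end-of-radiotherapy XQ comparison is an ANOVA without covariates although arms are minimised within site; the test is conservative and gives up available precision, and no unconditional adjusted test at that visit is planned.

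*Supplement*

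**What the plan says.** All references are to the Final Protocol.

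- **The test.** C.6, a. Data analysis: "All three arms will be compared at this time point using an analysis of variance, and if the test is significant", Duncan's Multiple Range Test then separates the arms. No covariate is attached to either step. The role of this visit is given as "For sample size justifications, our primary time endpoint is the end of radiotherapy, or 7 weeks".
- **Allocation.** C.3: "Patients will be randomized by a form of adaptive randomization, called minimization". Further, "the patient characteristics used for group assignment will be stage of disease, age (running mean), sex, the mean planned parotid doses" for the left and right gland separately, with induction therapy and concurrent chemotherapy added. Also: "Randomization will be conducted at each site separately".
- **Available data.** C.6 a: "We will have information available at baseline and at 5 additional points in time", so baseline XQ is in hand.
- **The plan's principle.** C.6 a: "inference about treatment effects has to appropriately adjust for recorded baseline characteristics of the enrolled patients". In the mixed models, which list XQ as the primary criterion variable, "baseline measures will be included as covariates", and the variables used for adaptive allocation are added. Tests of intervention at individual visits follow only if the intervention-by-time interaction is significant.
- **Which analysis is primary.** C.6 c. Sample size calculations calls the covariate-adjusted mixed model across post-intervention visits the primary analysis.
- **Site** is not named as a covariate in any model.

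**The concern.** Minimisation removes chance differences between arms in the factors it uses. A one-way ANOVA does not know this: it leaves the variation due to those factors in the residual. If the factors predict XQ, the residual variance overstates the true uncertainty of the arm differences. Standard errors are then too large, p-values too large and confidence intervals too wide. Running the allocation separately at each site does the same for any difference in mean XQ between sites.

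The factors are likely to matter to some degree. Section A (Significance) ties xerostomia to radiation exposure of salivary tissue, and planned parotid dose supplies two of the seven factors. The sites differ in country and in main tumour type.

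If the treatment effect is steady over time, the interaction need not be significant. The ANOVA is then the only comparison planned at the end of radiotherapy, and it is the unadjusted one.

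**Working it through.** **1. The plan's own figures (C.6 c).** Two-sided 0.05, 0.4 SD, 100 evaluable per arm, independent two-sample comparison, no covariates:

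- Power = Φ(0.4 × √(100/2) − 1.96) = Φ(0.868) = 80.7%.
- n per arm for 80% = 2 × (1.96 + 0.8416)² / 0.4² = 98.1, so 99 against 100 stated.
- At two-sided 0.01 and 0.49 SD: Φ(0.49 × √50 − 2.576) = 81.3%.
- Enrolment: 300 / (1 − 0.31) = 434.8, so 435.

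The stated figures are met without any gain from covariates.

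**2. Precision forgone.** Let R² be the share of end-of-radiotherapy XQ variance explained by the variables balanced at allocation, including site. The documents give no value, so a range is used. The adjusted standard error is √(1 − R²) times the unadjusted one: 0.98 at R² 0.04, 0.95 at 0.10, 0.92 at 0.16, 0.89 at 0.20.

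Site counts towards R². With two sites of similar size and a gap of Δ within-site SDs, site alone gives (Δ²/4) / (1 + Δ²/4). That is 0.0625/1.0625 = 0.06 for Δ = 0.5 and 0.25/1.25 = 0.20 for Δ = 1.

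**3. Effect on the three-arm test.** With the variables exactly balanced, the unadjusted F is close to (1 − R²) times the adjusted F. The 5% critical value on 2 and 297 df is 3.026. With one arm 0.4 total SD from the other two, λ = 100 × 0.4² × 2/3 = 10.67. Hence:

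- true type I error of the ANOVA = P(F > 3.026/(1 − R²));
- ANOVA power = P(noncentral F with λ/(1 − R²) > 3.026/(1 − R²));
- adjusted power = P(noncentral F with λ/(1 − R²) > 3.026).

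| R² (assumed) | Type I error, ANOVA | Power, ANOVA | Power, adjusted | Difference (points) |
|---|---|---|---|---|
| 0.04 | 4.4% | 84.0% | 85.3% | 1.2 |
| 0.10 | 3.6% | 84.5% | 87.6% | 3.0 |
| 0.16 | 2.8% | 85.1% | 89.8% | 4.7 |
| 0.20 | 2.4% | 85.5% | 91.2% | 5.8 |
| 0.25 | 1.9% | 86.0% | 92.9% | 6.9 |
| 0.36 | 1.0% | 87.4% | 96.2% | 8.8 |

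**4. Check by simulation.** Twenty thousand trials per setting with one balanced factor gave type I error of 4.5%, 3.5%, 3.0%, 1.8% and 1.0% at R² 0.04, 0.09, 0.16, 0.25 and 0.36. Power (ANOVA against adjusted) was 84.5% and 87.3% at 0.09, and 85.0% and 89.6% at 0.16. A separate simulation ran minimisation itself on seven factors within two sites of 133 and 167 patients (the planned 193:242 scaled to 300). It gave 84% against 87% at 10% of variance, and 84% against 91% at 20%. The formulas and both simulations agree on direction and size.

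Baseline XQ is not part of this arithmetic. Minimisation does not balance it, and any gain from it would come on top.

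**The case against.** **The primary XQ analysis is already adjusted.** A reader might infer from the ANOVA that the trial's main XQ inference ignores baseline and allocation factors. The documents do not support that: C.6 c calls the adjusted mixed model primary, C.6 a includes XQ in it, and the phrase about a primary time endpoint is limited to sample size. This stands, and it narrows the point to the end-of-radiotherapy comparison. It does not remove it, because the adjusted test at that visit depends on an interaction test and because site is not among the listed allocation characteristics.

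**Nothing false can be claimed.** A reader might take the p-values to be misleading in either direction. They err only towards caution, with type I error at or below 5%.

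**Power is not below target.** A reader might infer that the trial falls short of 80%. It does not. An unadjusted figure of 76% can be produced with 30% of variance explained and a site gap of 1 SD, but only if the effect is held at 0.4 of the within-site SD. The site gap raises the total SD to about √1.25 = 1.12, so that effect is only 0.4/1.12 = 0.36 total SD. With 0.4 read as total SD, the natural scale for an ANOVA that pools sites, unadjusted power in that setting is about 86 to 89%.

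**The size rests on assumed inputs.** This also stands. R² and the site gap appear nowhere in the documents. C.2 requires at least 24 Gy to one parotid gland, which narrows the dose range. It also excludes prior xerostomia, which may leave baseline XQ a weak predictor. At R² 0.04 the loss is only about one point.

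**Conclusion.** The point holds as a matter of efficiency and coherence at one visit. As written, the end-of-radiotherapy comparison uses neither the baseline value nor the allocation factors nor site, contrary to the plan's own principle of adjustment, and no unconditional adjusted test is planned there.

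The cost is a conservative test: about 3 points of omnibus power at R² near 0.10 and about 5 to 7 points at 0.16 to 0.20, with true type I error of about 2.5 to 4%. The direction follows from the allocation method once the factors or site predict XQ. The size depends on the assumed R², near-exact balance, 100 evaluable patients per arm and an effect of 0.4 total SD. The planned 80% power is kept, and the mixed model named as primary is not affected except that it omits site.

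**What to change.** In C.6 a, replace the ANOVA and Duncan's test at the end of radiotherapy with one of the following:

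- an end-of-radiotherapy contrast from the XQ mixed model, estimated whether or not the group-by-time interaction is significant; or
- an ANCOVA at that visit.

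In either case list the covariates: baseline XQ, site, stage, age, sex, left and right mean planned parotid dose (preferably continuous), induction therapy and concurrent chemotherapy. Take the three pairwise contrasts from that model. Add site to the longitudinal model by name.

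The yearly interim comparison of XQ change scores subtracts baseline but names neither site nor any allocation factor. It should use the same covariates.

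The cost is a change of wording in the analysis plan. Every covariate is recorded before or at randomisation, so no new data are needed.

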#### SECONDARY AIMS

1. Examine group differences in salivary flow rates using unstimulated and stimulated whole saliva flow rates. This will provide a more objective measure of salivary function.
2. Determine if true acupuncture is more effective than sham acupuncture or standard care for reducing the incidence of radiation-induced xerostomia.
3. Examine whether true acupuncture results in better overall quality of life than sham acupuncture or standard of care.
4. Determine acupuncture's effects on saliva-based factors including pH, buffer capacity, and viscosity as well as levels of total protein and the neuropeptides calcitonin-gene-related peptide (CGRP) and vasoactive intestinal polypeptide (VIP).
5. Examine the role of expectancy for the benefits of acupuncture in predicting outcomes. The role of expectancy as a moderator of the effects of treatment will be thoroughly examined.

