At each acupuncture visit, vital signs (blood pressure, pulse) will be taken, and medications will be reviewed prior to the acupuncture treatment. Since the SC group does not receive acupuncture, they will not have vital signs taken and medications will not be reviewed on a weekly basis. All measures will be collected again during the course of radiation treatment (mid-treatment; except the assessment of salivary constituents), at the end of the radiation treatment period, and at 2-4, 5-9, and 10-15 months. These assessments may be collected over the phone if the patient is unable to come to MD Anderson. Patients will also be asked to complete a form about their oral hygiene. All patients will be provided with standard oral care recommendations. These include keeping their mouth clean by brushing their teeth at least two times a day and preferably after each meal. They will be also encouraged to not use candies, lozenges, or drink sugary beverages. They will also be told to consume up to 1.5 liters a day of water to help diminish the effects of radiation-induced xerostomia and keep hydrated.

Follow-up assessments will be obtained 2-4, 5-9, and 10-15 months after the end of radiation treatment for a total of 6 assessments (baseline; middle of radiotherapy; end of radiotherapy; and 2-4, 5-9, and 10-15 months after the end of radiation treatment). Participants will be given a small gift certificate (100 RMB [approximately \$15] value at Fudan Cancer Hospital; \$35 value at M. D. Anderson) for completing each assessment. After all data are collected at the 12-month follow-up visit, patients in the G2 and G3 study arms will be offered true acupuncture treatment for free for one week (3 treatments). For the complete study schema, schedule, and timeline please see Appendix D. All data collection will be conducted by research staff who are blinded to group assignments. A procedures manual will be developed that will include all aspects of conducting the trial, including the acupuncture treatments.

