points. Post-intervention follow-up criterion measures will be regressed onto study intervention condition, time of assessment, a polynomial function of time (for example, quadratic) if appropriate, and the measure of the criterion at baseline. In addition, we will add important covariates, including adaptive randomization variables and selected demographic variables, such as ethnicity and education, as well as suitable baseline health-related variables and medical characteristics. Tests of the interaction of intervention condition with time of measurement will be evaluated to determine whether the effect of intervention condition varied as a function of time. In the case of statistically significant interactions of intervention condition with time, tests of the effect of intervention condition will be conducted at each individual time point. We will use Bonferroni corrections for each set of multiple comparisons where appropriate. Standard methods of model diagnostics will be used to identify influential observations and to determine suitable transformations where necessary.

We will compare compliance with acupuncture between patients randomized to the acupuncture and sham acupuncture groups. Compliance will be measured as the number of times the participants received their scheduled intervention per week. At each assessment after the end of radiotherapy, we will determine if patients in the two groups differ in the number of times they received their scheduled intervention (since the last analysis) using a Wilcoxon rank-sum test. We expect that these frequencies will not be normally distributed so we plan to use a nonparametric test. If there is a statistically significant difference or trend for significance in compliance between any two groups ( $p < 0.10$ ), we will also determine if there is a difference between other outcomes. We will use either t-tests or nonparametric tests such as the Wilcoxon rank-sum test to determine the significance of these differences.

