#### **c. Sample size calculations**

These precision and power estimates are based on a final post-intervention sample size of 300 study participants, 100 in each of the three intervention groups. To achieve this post-intervention sample size, we will oversample by 31% (i.e., 435 participants) to account for attrition. That is, we will allow for up to a 31% drop- out rate.

Our primary analysis is a mixed model regression analysis with repeated measures to evaluate the between group differences across the post-intervention time points with adjustment for covariates. Assuming a two- sided significance level of 0.05, we will have at least 80% power to detect differences between any pair of group means of 0.4 standard deviation units (SD – Effect Size Index) across the three post-intervention time points. In addition, the detectable mean difference between groups is 0.49 SD units with a two-sided significance level of 0.01. In our previous study, we found differences on post-intervention XQ means ranging from 0.80 SDs at the end of radiotherapy to 0.68 SDs at 1 month when comparing the acupuncture group with the standard care group. The associated XQ average values for the two groups at 1 month post radiotherapy were: 32.2 (SD=10.6) for acupuncture group and 41.5 (SD=9.6) for control group. As we do not know the exact differences that will occur between the sham acupuncture group and the other two groups, and given the definition of clinically significant effects (i.e., effect sizes of approximately 0.5 SDs being argued to be clinically meaningful) (25, 86, 87) the current study is still well-positioned to detect clinically significant effects between groups that may be present. We prefer to justify sample size using a paired t-test for simplicity and because it is conservative approach, although the later analyses using repeated measures will have greater power to detect differences between groups.

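### Holm's step-down method on the same tests would replace single-step Bonferroni at no cost in family-wise error, and the incidence family needs defining: a free improvement, not an error

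*Supplement*

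**What the plan says.** All references are to the final protocol, section C.6 a (Data analysis), unless noted.

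- Incidence is tested on two binary endpoints, each by a binomial test at each follow-up: CTCAE v3.0 xerostomia of grade 1 or higher, and an XQ score of 30 or less.
- The multiplicity rule follows the XQ criterion. It is conditional, "However, if 15 tests are made", and continues that "the significance level would need to be 0.003 or less (0.05/15) using a conservative Bonferroni method". The 15 tests are not listed.
- XQ is available at baseline and "at 5 additional points in time". There are three arms, with "100 in each of the three intervention groups" evaluable (C.6 c).
- The secondary aim is to "Determine if true acupuncture is more effective than sham acupuncture or standard care for reducing the incidence of radiation-induced xerostomia". The analysis section repeats the goal as whether the proportion with xerostomia "in the true acupuncture group is less than that in the sham acupuncture group or the standard care group".
- For tests at individual time points after a significant group-by-time interaction in the mixed models, the rule is: "We will use Bonferroni corrections for each set of multiple comparisons where appropriate".
- No step-down method appears anywhere in the final plan.

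**The concern.** Single-step Bonferroni compares every p-value with the same threshold, however many other hypotheses have already been rejected. Holm's method uses that threshold for the smallest p-value only and relaxes it after each rejection. Its family-wise guarantee is the same and needs no added assumption. If true acupuncture reduces the share of patients with an XQ above 30, the plan's rule will miss some time points that Holm would detect.

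The plan also does not say which tests make up the family. The natural reading of 15 is three pairs of arms at five post-baseline times. On that reading a third of the tests compare sham with standard care, a pair that the incidence aim does not name. The contrast most affected is true versus sham, for which the plan admits (C.6 c) that it does not know the expected difference.

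**Working it through.** **1. The plan's threshold.** 0.05/15 = 0.00333, printed as 0.003. Used literally, 0.003 is slightly stricter: 15 × 0.003 = 0.045.

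**2. Where 15 may come from.** Three arms give 3 pairs, and 3 × 5 times = 15 for one endpoint. This is an inference; the text does not state it.

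**3. Holm against Bonferroni on a fixed family of m tests.** Order the p-values. Compare the smallest with 0.05/m, the next with 0.05/(m−1), and so on, stopping at the first failure. For m = 15 the thresholds run 0.00333, 0.05/14 = 0.00357, up to 0.05. Each is at least 0.05/15, so any test that Bonferroni rejects is also rejected by Holm.

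**4. Size at a modest effect (simulation).** Assumptions:
- 100 patients per arm and 4,000 simulated trials.
- Control XQ means of 38, 54, 40, 34 and 31 at mid-radiotherapy, end of radiotherapy, and 2-4, 5-9 and 10-15 months.
- SD 10, near the pilot's 10.6 and 9.6 (C.6 c).
- Within-patient correlation 0.7^(lag^0.7).
- True arm 5 points below both controls at every time. This is 5/10 = 0.5 SD, the size that C.6 c calls clinically meaningful.
- Two-sided pooled z tests of XQ above 30.

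| Rule | True vs sham at 2-4 / 5-9 / 10-15 months | Family-wise error, no effect |
|---|---|---|
| Bonferroni, 15 tests | 34 / 45 / 44% | 3.4% |
| Holm, same 15 tests | 36 / 47 / 47% | 3.4% |
| Holm, 10 true-acupuncture tests | 45 / 55 / 56% | 3.4% |

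Holm alone gains 2 to 3 points per test. The further step to the third row needs a decision to narrow the family.

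**5. A second scenario.** Assume response-failure rates of 60% in the true arm against 80% in both controls at all five times, with latent correlation 0.5 and 6,000 runs. Mean per-test power for true versus sham goes from 0.566 (Bonferroni, 15) to 0.621 (Holm, same 15). The chance of at least one true-acupuncture rejection is unchanged at 0.985. The chance of a false rejection for sham versus standard care rises from 1.7% to 2.8%. Holm uses slack that Bonferroni leaves, and stays below 5%.

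**6. Size at the pilot rates (C.9 and C.10).** Power = Φ{[|p1−p2| − z·√(2p̄(1−p̄)/n)] / √[(p1(1−p1)+p2(1−p2))/n]}, with n = 100 and z = 2.935 at 0.05/15.
- Week 11, 60.0% vs 88.4%: p̄ = 0.742, so (0.284 − 2.935 × 0.0619)/0.0585 = 1.75 and power is 96.0%. At 0.05/10 it is 97.0%.
- Six months, 27.6% vs 63.6%: p̄ = 0.456, so (0.360 − 2.935 × 0.0704)/0.0657 = 2.33 and power is 99.0%. At 0.05/10 it is 99.3%.

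No method can add more than 100 − 96.0 = 4.0 points and 100 − 99.0 = 1.0 point here.

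**7. Two endpoints.** If CTCAE and XQ share one family, two contrasts × 5 times × 2 endpoints = 20 tests (0.05/20 = 0.0025). Three pairs give 30 tests (0.05/30 = 0.00167). Used for either family, 0.05/15 gives an error bound of 20 × 0.00333 = 0.067 or 30 × 0.00333 = 0.10.

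**The case against.** Bonferroni is valid, the plan itself calls it conservative, and the affected tests are secondary. The plan also has a mixed-model analysis of incidence that tests the overall treatment effect, so the aim does not rest on the separate tests alone. The XQ comparison of means at the end of radiotherapy uses analysis of variance followed by Duncan's test, so the Bonferroni rule does not govern it. All of this stands, and it keeps the point small.

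Three stronger readings are tempting, and the documents do not support them.

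- *The plan wastes error on five sham-versus-standard-care tests, with no gain in error control.* The make-up of the 15 is inferred from a conditional sentence. If those five tests are made, 0.05/15 protects them, and C.10 gives a reason to make the comparison: it wants a larger trial to establish that sham behaves like standard care. For the ten true-acupuncture tests alone, the bound falls from 0.05 to 10 × 0.00333 = 0.033. The claim of no gain holds only for Bonferroni against Holm on the same tests.
- *The divisor is simply too large.* With two binary endpoints it may be too small (step 7 of the working).
- *Only the three follow-ups should count, which would give six tests.* C.3 does say "Follow-up assessments will be obtained 2-4, 5-9, and 10-15 months after the end of radiation treatment", but dropping the other times would make the end of radiotherapy descriptive. C.6 a names that as the primary time endpoint for sample size. This is a substantive trade-off, not a free gain.

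**Conclusion.** The point holds as a free improvement. On any fixed set of tests, Holm keeps the plan's family-wise error and never rejects less than Bonferroni. That needs no assumption about effect size or about what the 15 tests are.

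The size does depend on assumptions. Over the same 15 tests, Holm adds 2 to 3 points per true-versus-sham test in the 0.5 SD scenario, and about 5 to 6 points on average in the 60% versus 80% scenario. At the pilot rates the gain is little. Those rates compare acupuncture with standard care, so they may flatter true versus sham. Narrowing the family to the ten true-acupuncture tests brings the total gain to about 10 to 12 points in the 0.5 SD scenario (45−34, 55−45, 56−44), but that is a choice for the sponsor. Lowering the Bonferroni divisor from 15 to 10 adds one point or less at the pilot rates.

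The undefined family is the other part of the point. Until the endpoints, contrasts and times are listed, a reader cannot tell whether 0.05/15 is stricter or more lenient than intended.

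**What to change.** In C.6 a:

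1. In the incidence paragraph, replace Bonferroni with Holm at 0.05 and list the tests in the family by endpoint, contrast and time point.
2. State that CTCAE grade 1 or higher and XQ of 30 or less are each their own family, or count both in one.
3. Optionally, limit the confirmatory family to true versus sham and true versus standard care at all five post-baseline times (10 tests per endpoint). Report sham versus standard care with confidence intervals, which suit a question of similarity better than a non-significant test. Keep the end of radiotherapy in the family.
4. In the mixed-model paragraph, replace Bonferroni with Holm and name the set of comparisons that it covers.

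The cost is wording only, with no change to sample size or data collection. Under item 3, sham versus standard care becomes descriptive for incidence. Simultaneous confidence intervals that match Holm's decisions are less simple than Bonferroni intervals, so the plan should say which intervals will be reported.
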